### **Session Plan for Art Therapy Intervention:**

First Session: Warm-up Exercise: Introduction to Colors Main Exercise: Paper Collage or Images – Creating a Family Tree, Depicting Current State Relaxation Exercise: Listening to Instrumental Music and Relaxation Purpose: Familiarity with group members, Self-expression Duration: 90 minutes

Second Session: Warm-up Exercise: Color Spots Main Exercise: Full-length Image, Painting Worst Fears & Threatening Situations, Stress Ballooning Relaxation Exercise: Closing Eyes and Imagining a Calming Place Purpose: Expressing Anger, Fear, Stress Duration: 90 minutes

Third Session: Warm-up Exercise: Contrasting Colors, Lines, and Shapes Main Exercise: Pockets and Boxes – Self-portrait, Symbolic Representation of Talents or Abilities, Drawing a Support Circle and Peaceful Painting Relaxation Exercise: Looking in the Mirror and Showing Self-compassion Purpose: Self-worth, Abilities, Support Duration: 90 minutes

Fourth Session: Warm-up Exercise: Creating Personal Symbol with Clay Main Exercise: Making Seasons with Clay, Creating a Nest Tree and Bird and Storm-affected Tree, Writing a Letter to God and a Letter to Spouse Relaxation Exercise: Breathing and Music, Gratitude Purpose: Insight, Solutions, Hope and Future Duration: 90 minutes

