4. State-Trait Anxiety Inventory – A self-report psychometric scale measuring two distinct but related concepts of anxiety. Situational anxiety refers to consciously perceived emotional situations causing tension, fear, restlessness, worry, and increased nervous system activity. Personal trait anxiety is individual differences in the disposition to perceive or evaluate stressful situations as threatening or dangerous. Responses to these situations lead to increased anxiety (Lotfi Afshar, 1997).

Initially, women will complete the grief questionnaire, and if individual grief is confirmed, they will be included in the study. The intervention group will receive two sessions per

week, totaling four 90-minute art therapy sessions following a designed protocol. The participants will complete the anxiety, grief, and quality of life questionnaires are completed by participants at the beginning of the study. After 2 weeks of intervention and at the end of the intervention, the grief and anxiety questionnaires are completed again. Eight weeks after the intervention, all three questionnaires will be completed by participants. Upon entry into the study, participants will respond to the quality-of-life questionnaire. They will also respond to the quality-of-life questionnaire with a 4-week interval from the end of the intervention, both before and after the intervention, with a 2-week interval between assessments. The scores before and after the intervention will be compared using paired t-test.

No interventions will be made for the control group during the study period. However, after this time and for ethical considerations, if participants in the control group desire, a more condensed session (2 sessions) with the same content will be held for the control group.

Registration General, Specific, and Practical Objectives Main Objectives of the Plan:

- Determining the effect of art therapy on anxiety and quality of life following pregnancy loss in women attending hospitals affiliated with Tehran University of Medical Sciences in 2019.

Subsidiary Objectives of the Plan:

- Comparing the average grief score following pregnancy loss in the intervention and control groups at the beginning, after two intervention sessions, at the end of the intervention, and 8 weeks after the completion of the intervention in women attending hospitals affiliated with Tehran University of Medical Sciences in 2019.

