#### **Implementation Method:**

**Study Type:** The present study is a parallel randomized clinical trial involving 60 mothers (30 in the intervention group and 30 in the control group) who attend the hospitals of Tehran University of Medical Sciences following pregnancy loss. Individuals who meet the inclusion criteria, including a history of recent miscarriage or stillbirth within the last 6 weeks, having at least basic literacy skills, willingness to participate in the study, confirmation of grief using the PGS questionnaire, and residing in Tehran, will be enrolled in the study. At the beginning of the visit, the Perinatal Grief Scale (PGS) will be completed by the participants. Those scoring 92 or higher on the total grief score, or 34 or higher on the active grief or 30 or higher on the difficulty coping subscale, or 27 or higher on the despair subscale, indicating high levels of grief, will be included in the study.

**Randomization Method:** This will be carried out using a block randomization method. Four-person blocks are selected so that Group A will be the intervention group and Group B will be the control group. Each of the six possible scenarios will be written on separate cards, numbered from one to six. The numbers will then be written on paper, randomly selected, until the expected number of samples is complete. The concealment of the sequence will be done using sealed envelopes, each containing one of the designated letters in order, sealed, and given to the researcher. The randomization and concealment process will be performed by a statistical consultant.

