**Blinding Procedure:** Due to the nature of the intervention, blinding is not feasible. Subsequently, participants will be informed about the study and will complete an informed consent form. Demographic, grief, anxiety, and quality of life questionnaires will be completed by them. The selected samples will undergo four 90-minute sessions of art therapy and pottery weekly for two weeks according to the designed program detailed below, and anxiety and grief questionnaires will be completed after two sessions of art therapy and at the end of the intervention. Eight weeks after the intervention, the questionnaires will be completed again. During the intervention period, the control group will not receive any art therapy interventions, except for routine medical care following pregnancy loss. To ensure research ethics, all participants will be assured of the confidentiality of the research results. Additionally, after the intervention period, a condensed intervention (2 sessions) will be offered to the control group if the individuals are willing. To combat Miss to follow up issues, participants will be reminded of their class attendance one day before each art therapy session through SMS messages. The completion of questionnaires eight weeks after the intervention will be done electronically.

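### Art therapy appears to be given in groups to individually randomised women, but the only named test has no term for group; if outcomes correlate within groups, standard errors are too small and the type I error exceeds its nominal level

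*Protocol*

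**What the plan says.** The protocol (Implementation Method) plans "60 mothers (30 in the intervention group and 30 in the control group"). Randomisation is by individual woman: "Four-person blocks are selected so that Group A will be the intervention group and Group B will be the control group". During the intervention period, "the control group will not receive any art therapy interventions, except for routine medical care following pregnancy loss".

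Two places point to group delivery of the art therapy. In the Session Plan for Art Therapy Intervention, the first session is described as "Purpose: Familiarity with group members, Self-expression Duration: 90 minutes". In the Implementation Method, under the blinding procedure, "participants will be reminded of their class attendance one day before each art therapy session". One-to-one delivery is described nowhere. The number and size of the groups, the number of therapists and any expected within-group correlation are not given.

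On analysis, the Summary of Implementation Method and Analysis Approaches names one test: "The scores before and after the intervention will be compared using paired t-test". The subsidiary objectives in the same section call for comparisons between arms, for example "Comparing the average grief score following pregnancy loss in the intervention and control groups at the beginning, after two intervention sessions", but no between-arm test or model is named and no significance level is stated. The data collection tools listed there are a demographic form and three scales; therapy group is not among them.

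**The concern.** Women who attend the same sessions share peers, dates and possibly a facilitator, and getting to know one another is a stated aim of the first session. Their later grief, anxiety and quality-of-life scores may therefore resemble one another more than those of women in different groups. Controls have no such structure, so this is a partially nested design, with clustering in one arm only.

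A t-test that counts the 30 art-arm women as 30 independent observations then uses too small a variance for that arm's mean. Confidence intervals come out too narrow and p-values too small, which favours a false claim of benefit. In an unblinded trial with self-reported outcomes and 30 women per arm, a further push in that direction is worth removing.

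**Working it through.** **Inputs from the protocol.** 30 women per arm; individual randomisation; art therapy apparently in groups; controls on routine care; paired t-test as the only named test. The sample size of 60 comes without power, effect size, standard deviation or significance level, so there is no figure of the plan's own to reproduce on this point.

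**Assumptions.** Group size m of 6, 10 or 15 (five, three or two groups in the art arm). ICC of 0, 0.01, 0.02, 0.05 or 0.10. Nominal two-sided 5%. Equal total variance in the two arms, and controls ungrouped up to the assessment analysed.

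**Formulae.**
- Design effect in the art arm: DE = 1 + (m − 1) × ICC.
- Between-arm comparison: only one of the two arm variances is inflated, so the variance of the difference is understated by (DE + 1)/2 and the standard error by √[(DE + 1)/2]. True error of the ordinary t-test ≈ 2 × [1 − Φ(1.96 / √((DE + 1)/2))].
- Paired t-test within the art arm, with the ICC applying to change scores: true error ≈ 2 × [1 − Φ(1.96 / √DE)].

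**One case in full.** For m = 10 and ICC = 0.05, DE = 1 + 9 × 0.05 = 1.45. Between arms, (1.45 + 1)/2 = 1.225 and √1.225 = 1.107; 1.96/1.107 = 1.771, giving 7.7%. For the paired test, √1.45 = 1.204; 1.96/1.204 = 1.628, giving 10.4%.

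**Results.** Each cell shows the factor by which the standard error should be larger, then the true type I error.

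Assumed between-arm t-test:

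| ICC | m = 6 | m = 10 | m = 15 |
|---|---|---|---|
| 0 | 1.00; 5.0% | 1.00; 5.0% | 1.00; 5.0% |
| 0.01 | 1.01; 5.3% | 1.02; 5.5% | 1.03; 5.8% |
| 0.02 | 1.02; 5.6% | 1.04; 6.1% | 1.07; 6.6% |
| 0.05 | 1.06; 6.5% | 1.11; 7.7% | 1.16; 9.2% |
| 0.10 | 1.12; 8.0% | 1.20; 10.4% | 1.30; 13.3% |

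Named paired t-test within the art arm:

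| ICC | m = 6 | m = 10 | m = 15 |
|---|---|---|---|
| 0 | 1.00; 5.0% | 1.00; 5.0% | 1.00; 5.0% |
| 0.01 | 1.02; 5.6% | 1.04; 6.1% | 1.07; 6.6% |
| 0.02 | 1.05; 6.2% | 1.09; 7.1% | 1.13; 8.3% |
| 0.05 | 1.12; 8.0% | 1.20; 10.4% | 1.30; 13.3% |
| 0.10 | 1.22; 11.0% | 1.38; 15.5% | 1.55; 20.6% |

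Simulation of 40,000 trials per setting, with 30 per arm and t-tests on the usual degrees of freedom, agreed with the formulae to within 0.3 percentage points wherever it was run (all settings except ICC 0.02). For example, at m = 15 and ICC 0.10 the simulated between-arm error was 13.5%. The paired test fares worse because no unclustered control arm dilutes the inflation.

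**The case against.** The strongest reply is that the protocol names no between-arm test, and that the model for the treatment comparison, including any term for therapy group, may properly stand in a SAP. That is right as far as it goes: the between-arm figures are for an assumed analysis, and the protocol cannot be faulted for an inflated between-arm error that it never specifies. But it does name a test, and that test ignores grouping. This is a stated choice, not silence.

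A second reply is that the inflation is conditional. This stands in full. A reader might infer that the type I error is above 5% as a matter of fact. The documents do not support that: at ICC 0 the error is 5.0% whatever the group size, at ICC 0.01 it is under 6% between arms, and the protocol gives neither ICC nor group size. The top of the between-arm range needs ICC 0.10 and only two groups of 15, which nothing in the protocol establishes. Closed groups with fixed membership are not stated either, and if one therapist ran every session, the therapist would not add to variation between groups.

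A reader might also infer that the problem could never be repaired, because therapy group is not among the listed data. That does not follow. The list covers questionnaires, not session records, and sending a reminder before each session requires someone to know which woman attends when. Group membership may well be recoverable.

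Finally, a paired before-after test does not answer the between-arm objectives in the first place. That is a separate defect. Correcting it with an ordinary two-sample test would still leave the grouping unaddressed.

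**Conclusion.** The point holds in conditional form. Group delivery is a fair inference from the session plan and the reminder text, clustering would arise in the art arm only, and the one named test treats women as independent. If within-group correlation is positive, standard errors are too small and the error rate is above nominal.

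The size depends wholly on assumed values. For groups of 6 to 15 and ICC up to 0.10, the between-arm error runs from 5.0% to about 13%, and that of the named paired test from 5.0% to about 21%. At small ICC the effect is minor; with groups of 10 and ICC 0.05 it is large enough to change a borderline conclusion. The change is worth making because it is cheap and the error, where present, favours the intervention.

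**What to change.** 1. State in the protocol whether sessions are held in groups and, if so, the planned size and number of groups, and record the therapy-group number for each art-arm woman.
2. In the between-arm analysis that the objectives require, allow for clustering in the art arm only: a partially nested mixed model with a random effect for therapy group in that arm and small-sample degrees of freedom.
3. With perhaps two to five groups, that random effect may not be estimable. In that case, report as a sensitivity analysis the between-arm confidence interval with the art-arm variance multiplied by 1 + (m − 1) × ICC for ICC 0.02, 0.05 and 0.10, using the actual group sizes.

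The cost is one data field, a slightly more complex model and somewhat wider intervals: by a factor of about 1.02 to 1.30 over the group sizes of 6 to 15 and the ICC values of 0.02 to 0.10 considered above. The fallback relies on assumed ICCs, so it shows how sensitive the conclusion is but does not settle it.

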### **Reducing Implementation Constraints:**

Intervention variables beyond control in this research include: mental and psychological status, cultural and social backgrounds, individual differences among patients, and the complexity of the grief issue in different individuals. These factors may impact the research results. Providing assurance to participants regarding the confidentiality of information can largely address this issue, but complete control is beyond the researcher's capabilities.

References:

- 1)Ekström A and Nissen E (2006) A mothers feelings for her infant are strengthened by excellent breastfeeding counseling and continuity of care. *Pediatrics*. 118 (2) e309-e14.
- 3) Davudsdottir, R. (2012). *Anthropology of Childbirth Cross-cultural approach*. Unpublished BA Thesis, University of island.
- 4) Goodman P, Mackey M C and Tavakoli A S (2004) Factors related to childbirth satisfaction. *Journal of Advanced Nursing*. 46 (2) 212-9.
- 5) M. Tomlinson P. J. Cooper A. Stein L. Swartz C. Molteno Post-partum depression and infant growth in a South African peri-urban settlement, *J: child:care, health and development*, January 2006
- 8) Myles textbook for midwives. Translated by Fatemeh Vasegh R. (2015).
- 9) Janati Y. (2013). *Psychiatry in midwifery*..
- 10). Helen Statham. The effects of miscarriage and other 'unsuccessful' pregnancies on feelings early in a subsequent pregnancy. *Journal of Reproductive and Infant Psychology*.Volume 12, 1994- Issue 1.
- 11)Evelyn Regina Couto, Quality of life, depression and anxiety among pregnant women with previous adverse pregnancy outcomes, *Sao Paulo Med. J.* vol. 127 no.4 São Paulo July 2009.  
<https://www.who.int/healthinfo/survey/whoqol-qualityoflife/en/2019>
